## Abstract

**Background:**

Many patients who have been treated for breast cancer experience high levels of fear that the cancer will return. The FORECAST pilot study showed that for a third of the patients, fears of cancer recurrence (FCR) increase during radiotherapy treatment and that conversations with their therapeutic radiographer at the weekly review meetings might help patients manage these concerns. This study aims to develop a communication skills training package (KEW, for ‘Know’, ‘Encourage’ and ‘Warm-up’) for therapeutic radiographers based on the findings of the FORECAST pilot study and on active input from patients and radiographers. This package will be piloted in a single centre to evaluate its acceptability and to prepare for a multi-centre clinical trial.

**Methods:**

The study consists of three phases. In the first phase, patient representatives and therapeutic radiographers participate in Experience-Based Co-Design to identify ways to improve communication during the radiotherapy review. In the second phase, various stakeholders, including members of the Society of Radiographers and of national patient representation groups, are consulted to develop a storyboard for the production of the communication training package. In the third phase, the acceptability and feasibility of the training is evaluated through observations, recruitment rates and follow-up discussions; a fidelity measure is designed; and potential benefits are observed, with patients’ fear of cancer recurrence (FCR7) as the primary outcome. Secondary outcomes include a short daily measure of recurrence (FCR3), patients’ positive and negative affect (PANAS), perceived empathy from the radiographer (CARE), satisfaction with the review meetings (RISS) and health-related quality of life (EQ-5D-3L).

**Discussion:**

To date, there has been limited research on how communication between therapeutic radiographers and patients during review appointments can help to manage patients’ recurrence fears during radiotherapy treatment. A collaborative and participatory approach to the development of a communication skills training will ensure that it is optimally targeted to the needs and preferences of both patients and radiographers. Targeting recurrence fears through communication at this stage, when patients are still in regular contact with healthcare providers, has the potential to reduce the need for complex interventions post-treatment.

**Trial registration:**

NRES reference: 18/LO/0669. Clinicaltrial.gov ID: NCT03468881

## Background

Breast cancer is the most common cancer in the UK, with 54,900 new cases every year [1]. Steadily improving survival rates also mean that the number of people who are breast cancer survivors is growing [2]. After treatment has finished, patients’ physical and psychological symptoms do not immediately end and survivors need to be supported to cope with the consequences of their treatment and with the concerns that they experience [3]. Often, breast cancer survivors are most concerned about the possibility of their cancer returning [4–6]: up to 86% of all breast cancer survivors experience some level of this fear, moderate levels are reported by 24 to 56%, and up to 14% of survivors experience high levels of recurrence fears [7].

Fear of cancer recurrence (FCR) has been defined as the ‘fear, worry, or concern relating to the possibility that the cancer will come back or progress’ [8]. High levels of FCR are associated with higher health costs [9] and have been linked to health behaviour and psychological responses such as distress, depression and anxiety [7]. Due to its high prevalence and serious consequences, it has been advised to carry out routine assessment for FCR following treatment [9]. To help patients who do experience clinical levels of recurrence fears, various psychological interventions have been developed, including Conquer Fear [10], SWORD (‘Survivors’ Worries of Recurrent Disease’) [11] and the AFTER intervention [12].

However, ideally, patients would be supported in such a way to minimise the development of these fears before they rise to clinical levels, which was the focus of the FORECAST pilot study [13]. The Lee-Jones model of FCR describes that in addition to patients’ internal cues, external cues such as communication with healthcare providers can trigger an emotional and cognitive response that result in patients’ personal perception of recurrence [14]. A recent study also found empirical evidence for the relation between such cues and FCR [15]. In addition, there is work that suggests that patients’ perceived quality of interactions during the diagnostic consultation can indeed affect their FCR levels [16].

FORECAST analysed conversations between 89 patients and their radiographers during the weekly review appointments and identified these sessions as a crucial target point—it was seen that patients whose FCR trajectories decreased during radiotherapy were more likely to mention cancer directly at the review appointments, had longer consultations, and expressed twice as many emotional concerns [17]. Furthermore, a significant relationship was seen between patients FCR levels and closing down of patients’ conversations in a clinical encounter during a review appointment in the radiotherapy unit. Since radiotherapy services for breast cancer patients often include a review service [18], this could be an optimal moment to address patients’ recurrence fears before they rise to excessive levels. The outlined protocol describes the follow-up to this study, FORECAST2 [19]. FORECAST2 builds upon the findings of the pilot study to develop a communication skills training package for therapeutic radiographers, to help them respond to emotional concerns that are expressed by patients at the review appointments. Theoretically, the package will be modelled on an intervention for general practitioners that successfully helped patients feel less distressed and more satisfied with the consultation [20] to target patient *Knowledge*, *Encouragement* to patients to express concerns and *Warm-Up* to avoid sudden cutoffs at the end of the conversations (KEW). In addition, patients and therapeutic radiographers will be actively involved in the development of the training package through *Experienced-Based Co-Design* (EBCD), to encourage the exchange of experiences between patients and healthcare providers and identify shared points for improvements and solutions [21].

The aims of the study outlined in this protocol are (1) to develop a communication skills training package for therapeutic radiographers and (2) to pilot this package in a single service. The evaluation will include the observation of potential benefits in practice, in particular the effect of the package on patients’ development of FCR trajectories. In addition, the single-service evaluation will help to prepare for a formal randomised trial by evaluating the acceptability and feasibility of presentation to staff and patients, completing electronic diary assessment of recurrence fears, and the design of a fidelity measure.

## Methods/design

This study consists of three phases (Fig. 1): a co-design, production and evaluation phase.

**Fig. 1 Fig1:**
[figure not shown]
Flowchart of outlined study, consisting of three consecutive phases

### Phase 1—Co-design

The aim of the first phase is to identify shared issues in communication during radiotherapy treatment with breast cancer patients and therapeutic radiographers and to work on solutions to help improve this communication. This exploratory phase of the study will be guided by principles of EBCD [22] and will make use of a variety of participatory methods, including card sorting to identify priorities, brainstorming to generate ideas and the emotional mapping exercise [23], in which patients can identify and rank critical moments in their radiotherapy treatment. Four patient representatives and three therapeutic radiographers will be recruited at a specialist breast cancer centre in Scotland through the investigators’ networks, based on willingness to participate. Eligible patient representatives are female, are over 18 years of age and have received radiotherapy to treat their breast cancer.

Phase 1 will start with introductory individual interviews with the patients and radiographers to identify their experiences with the radiotherapy service and to discuss improving communication (Table 1). The patient interviews will be filmed, and a short video will be edited to capture patient experience. This film will be validated at a patient feedback event and later shown at a joint patient-staff event as the starting point to share experiences and agree on areas for improvement. Prior to the joint event, radiographers will also have a feedback event to validate findings from the interviews and to distinguish between issues to be addressed internally and those to be discussed in the co-design process. After the video is discussed at the joint patient-staff event, a co-design session follows to work on solutions to the issues that are raised. All sessions that are not filmed will be audiotaped and can be transcribed to identify themes in participants’ responses using a thematic framework approach; emphasis will be on summarising and validating participants’ input during the sessions.

**Table 1 Tab1:** Topics discussed during sessions of phase 1

Interview radiographers	
Background about role	
Staff experiences	
Perceptions of patient experience	
Improving communication	
Feedback event radiographers	
Validation of findings from interview	
Distinguish between topics to be addressed ‘internally’ and for co-design	
Interview patients	
Journey so far	
Satisfaction with radiotherapy experience	
Crucial points in radiotherapy process	
Improving communication	
Feedback event patients	
Validation of findings presented in video	
Mapping and rating of key stages and moments; agree on topics to be discussed with staff	
Joint staff-patient event	
Exchange experiences (using video)	
Determine shared priorities	
Brainstorm to identify solutions	

### Phase 2—Production

The second phase of the outlined study works towards the production of a video and training manual for the communication training package. Based on the findings of phase 1, evidence on successful strategies to improve patients’ satisfaction with consultations [20] and on correlations between patient-provider interactions during review appointments and patients’ levels of FCR [17], the modules that will be covered in the training workshop will be determined and a storyboard will be created for the production of the training package. Examples of the types of communication interventions that are likely to be covered include open-ended general questions on how the patient is managing and how they are feeling, to listen to enquiries and provided additional information (*Knowledge*), to acknowledge emotional cues and prevent closing the patient down (*Emotion*) and to give a positive finishing statement on closing the review session (*Warmth*). The storyboard will be evaluated and adjusted in an iterative process with consultative input from a variety of stakeholders.

Participants in this phase will include up to ten members of patient representation groups throughout the country and a radiotherapy stakeholder group with eight members of the Society of Radiographers. Participants will be recruited through the networks of the authors based on willingness to participate. Inclusion criteria for patient participants are as described for phase 1 of the study. Based on the logistical feasibility, consultative input will be invited either through face-to-face interviews or through email, using the Feedback Capture Grid (Interaction Design Foundation). Face-to-face sessions will be audiotaped, and themes in participants’ responses will be explored as described for phase 1.

### Phase 3—Evaluation

The aim of the third phase of the study, an observational cohort study, is to evaluate the communication training package in a specialist breast cancer centre in Scotland. All women with breast cancer who undergo radiotherapy treatment at this centre are seen at the weekly review appointments (usually two to three times and up to four to five for patients with ductal carcinoma in situ), as follow-up appointments and GP letters are generated at these clinics. Therapeutic radiographers who are willing to participate will follow an in-person session with a trained facilitator using the communication skills training package. Written materials will be available with examples, and workshop experiential sessions will be provided, as well as supervision by a clinical psychologist and communication trainer.

The radiographers will screen for patient eligibility (i.e. adult, English-speaking, female invasive breast cancer patients about to receive radiotherapy as primary or adjuvant treatment) and invite patients to participate in the study (t_−1_) (Fig. 2). Patients who are interested to participate are referred to the investigator who will provide them with more information. Written informed consent is obtained from those who are willing to participate. Around the radiotherapy planning session (t_1_), patients are asked to provide their demographic details and to fill out the seven-item Fear of Cancer Recurrence (FCR7) measure and Positive And Negative Affect Scale (PANAS) (Table 2). During radiotherapy treatment, the regular weekly review consultations between the patient and therapeutic radiographer will be audiotaped (t_2_). During these 3 to 4 weeks, patients fill out FCR7 on a weekly basis and the three-item Fear of Cancer Recurrence (FCR3) on a daily basis, either in the form of a printed diary or in a smartphone application according to patient preference. At the end of radiotherapy (t_3_), patients fill out the FCR7 and PANAS again and evaluate their experience with the consultations using the Consultation and Relational Empathy (CARE) measure and the Radiotherapy Interview Satisfaction Scale (RISS), a version of the Medical Interview Satisfaction Scale modified to better fit the radiotherapy consultations. Six to eight weeks after the end of their treatment (t_4_), patients will receive a telephone call from the investigator to measure their recurrence fears (FCR7) one last time and their health status, using the EQ-5D-3L.

**Fig. 2 Fig2:**
[figure not shown]
Timeline of study enrolment and assessments of the evaluation phase (phase 3): after SPIRIT [34]

**Table 2 Tab2:** Instruments used in evaluation of patient outcomes and psychometric properties

Instrument	Measures	Properties
FCR7	7-item self-report measure of patients’ Fear of Cancer Recurrence	Internal consistency: Cronbach’s *α* of 0.92. Construct validity: *r* = 0.68 versus Anxiety Sub-scale of Hospital and Depression Scale [35]
FCR3	3-item self-report measure of patients’ Fear of Cancer Recurrence	Based on the 4-item scale FCR4, with internal consistency: Cronbach’s *α* of 0.93. Construct validity: *r* = 0.65 versus Anxiety sub-scale of Hospital and Depression Scale [35]
PANAS	20-item self-report measure of Positive And Negative Affect	Internal consistency: Cronbach’s *α* of 0.89 for Positive Affectivity; 0.85 for Negative Affectivity. Construct validity: *r* = 0.52 versus HADS depression sub-scale; *r* = 0.67 versus Depression Anxiety and Stress Scales (DASS) stress sub-scale and 0.65 versus HADS anxiety sub-scale [36]
RISS	8-item self-report measure of patients’ Radiotherapy Interview Satisfaction	Adapted from the Medical Interview Satisfaction Scale (MISS-21) with internal consistency: 0.67–0.92 for sub-scales. Construct validity: *r* = 0.21–0.63 versus aspects of satisfaction with consultations [37]
CARE	10-item self-report measure of patients’ experience of Consultation and Relational Empathy	Internal consistency: Cronbach’s *α* of 0.92. Convergent validity: *r* = 0.85 versus Reynolds Empathy Measure (RES) and sufficient face validity [38]
EQ-5D-3L	5-item self-report measure of patients’ health status relating to mobility, self-care, usual activities, pain and discomfort, and anxiety and depression	Well-established reliability and validity; used in many countries and for many different conditions [39, 40]

In addition to the observation of potential benefits relating to patient outcomes, the acceptability and feasibility of the communication training package is evaluated through analysis of the audiotaped sessions and follow-up discussions with patients and radiographers. A 10% sample of patients will be invited to give free response comments from semi-structured interviews to their experience of the review consultations. These patients will be prompted to state the acceptability (rating on a 1 to 5 ordinal scale from ‘not acceptable’ to ‘completely acceptable’) of the major elements of the intervention, e.g. staff instructed to give patient space to expand on a concern. Prompts will cover the various dimensions of ‘acceptability’ including content, complexity and comfort [24]. All staff will be invited to give a similar acceptability rating for each element and an overall score of the intervention. Free responses will be analysed using a thematic framework approach. To help prepare for a multi-centre randomised controlled trial, participant recruitment and retention rates will be calculated and a fidelity measure will be designed to evaluate the extent to which the training delivery and implementation of the trained communication skills follows the designed protocols.

### Data management

Data from paper questionnaires will be anonymised by replacing the participant’s name with a unique identifying code and saved in a password-protected database. Data will be coded and entered into SPSS 24. Storage and analysis will take place in a ‘safe haven’ at the University, a room with secure entry procedures dedicated to analysing audio-visual materials. The key with names and ID numbers will be stored in a secure location at the study site. After audiotaped conversations are transcribed and coded, all uniquely identifying information will be blanked out. Data that is collected through the mobile phone application will be visible for participants (via password-protected access to the mobile application to guard against view by third parties with access to the device) and sent to a storage server in the ‘safe haven’ using Transport Layer Security (version 3) when the participant’s phone is connected to WIFI or mobile phone signal. An AES 256-bit double-layer encryption system [25] will be used to store the data.

### Analyses

Audiotaped sessions from phases 1 and 2 will be transcribed and content analysed [26], using a hybrid strategy of inductive and deductive thematic analysis [27]. Consultations that are audiotaped in phase 3 will be analysed using the Verona coding definitions of emotional sequences (VR-CoDES) [28], as described in the FORECAST pilot study [17]. Latent variable growth curve analysis (MPLUS) will be used to determine patients’ FCR trajectories and link these to FCR7 outcomes. Patient outcomes from the outlined study, in which therapeutic radiographers have been exposed to the communication skills training package, will be compared to patient outcomes from the pilot study that took place prior to the introduction of the training package. The cohort of the FORECAST pilot study was drawn from the same institution; any differences will be controlled for statistically in a conventional method of covariate inclusion. Matching the sample size of the pilot study cohort, the aim is to recruit 74 patients so that an effect of 0.375 (medium to low) can be detected at 80% power with a two-sided alpha of 0.05, to evaluate the effect of the training package on FCR levels.

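### The target of 74 is said to match a pilot for which 89 analysed patients are reported, and with either number an unadjusted two-group comparison falls short of 80% power at 0.375

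*Protocol article*

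**What the plan says.** The primary patient outcome is FCR7 (Abstract, Methods: "with patients’ fear of cancer recurrence (FCR7) as the primary outcome"). The evaluation phase has no concurrent control group. Outcomes after the training "will be compared to patient outcomes from the pilot study that took place prior to the introduction of the training package" (Analyses). The same section describes that comparator only by its origin and by the adjustment to be made: "The cohort of the FORECAST pilot study was drawn from the same institution; any differences will be controlled for statistically".

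The recruitment target rests on the size of the pilot: "Matching the sample size of the pilot study cohort, the aim is to recruit 74 patients". The same sentence gives its justification, that "an effect of 0.375 (medium to low) can be detected at 80% power with a two-sided alpha of 0.05".

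The Background gives another number for the pilot: "FORECAST analysed conversations between 89 patients and their radiographers during the weekly review appointments". The article does not say how the 89 and the 74 are related.

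**The concern.** The pilot appears with two sizes, and the recruitment target is justified by matching one of them. The number of pilot patients with analysed conversations (89) is larger than the number given as the size of the pilot cohort (74). So 74 cannot be the whole pilot with the 89 drawn from within it. Either 74 is a particular set of pilot patients that the article does not name, or the target does not match the cohort.

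This bears on the power statement, because a comparison with a historical group depends on the size of both groups. A reader who wants to check the claim of 80% power must first know how many pilot patients contribute FCR7. Trying each candidate number shows that none of them supports the claim on the simplest reading. At stake is how a null or imprecise result would be read: a study believed to have 80% power for 0.375 would be given more weight than one with 62% to 66%. The estimate is also meant to inform a later randomised trial.

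**Working it through.** **Inputs.** New recruits: 74 (Analyses). Pilot patients: 74 (Analyses) or 89 (Background). Effect 0.375, power 80%, two-sided alpha 0.05 (Analyses). Assumptions: 0.375 is a difference in SD units, the comparison is two independent groups without adjustment, and all 74 recruits are analysed. The article states no loss allowance; the Phase 3 section says only that "participant recruitment and retention rates will be calculated".

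**The gap.** 89 − 74 = 15, and 15/89 = 16.9%.

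**Can the stated figure be reproduced?** The size per group for two equal groups is

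n = 2(1.960 + 0.842)² / 0.375² = 2 × 7.849 / 0.1406 = 111.6, so 112 (113 by the t-test).

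This is well above both 74 and 89.

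**Power and detectable effect by pilot size.** With SE = √(1/n₁ + 1/n₂), power ≈ Φ(0.375/SE − 1.960), and the effect detectable at 80% power is 2.802 × SE.

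| New v pilot | SE | Power, normal | Power, t-test | Detectable effect, normal | Detectable effect, t-test |
|---|---|---|---|---|---|
| 74 v 74 | 0.1644 | 62.6% | 62.0% | 0.461 | 0.464 |
| 74 v 89 | 0.1573 | 66.4% | 65.9% | 0.441 | 0.443 |
| 89 v 89 | 0.1499 | 70.6% | 70.1% | 0.420 | 0.422 |

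Example for 74 v 74: 0.375/0.1644 = 2.281; 2.281 − 1.960 = 0.321; Φ(0.321) = 0.626.

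With the pilot size fixed, the new recruits needed for 80% power at 0.375 are 1 / [(0.375/2.802)² − 1/n₂]. That is about 228 against 74 pilot patients and about 150 against 89.

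**Other readings tried.**
- One-sided test: 73.8% for 74 v 74. Only 89 v 89 reaches 80% (80.4%), but the article states a two-sided test and 74 recruits.
- 74 in total (37 v 37): 36.4%.
- One-sample test, with the pilot mean treated as known: 58 patients suffice, and 58/(1 − 0.20) = 72.5, so 73, is close to 74. But this is not the stated comparison, and no 20% loss is stated.
- Baseline-adjusted comparison, where the variance is multiplied by (1 − r²): the r that brings the detectable effect down to 0.375 is √[1 − (0.375/0.461)²] ≈ 0.58 for 74 v 74, and √[1 − (0.375/0.441)²] ≈ 0.53 for 74 v 89. No correlation is stated.

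**The case against.** The strongest reply has three parts.

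First, 89 and 74 may count different things. The Background figure counts patients in a conversation analysis. It is not called the cohort, the control group or the FCR7 outcome set, and the only figure attached to the comparator is 74. This stands. The difference is unexplained; it is not a proven contradiction.

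Second, the planned analysis is not an unadjusted t-test. The article plans latent growth curves on repeated FCR7 scores, with covariates for differences between the cohorts. Either could add precision, and a baseline correlation near 0.58 would be enough. This stands as a possibility. However, the sentence ties 74 to 0.375 without mentioning any such gain, so the claim holds only under an input that the reader is not given.

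Third, an article may leave the definition of analysis sets to the full protocol or analysis plan. This also stands. The exact inclusion rule for the pilot patients is not part of this point.

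A reader might go further and infer that 74 is the pilot subset with complete FCR data, so that new recruits are being set against a selected control group. Nothing in the article says so. Nor does it support taking 74/89 = 83% as a usable-data rate and projecting about 62 analysed recruits (74 × 0.831 = 61.5). A reader might equally infer that using all 89 would gain power at no cost, but that requires FCR7 outcomes for the other 15, which are not reported. The last two inferences also conflict: if the 15 lack usable FCR7 data, they cannot enlarge the comparator.

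**Conclusion.** The power statement is wrong as written, on the assumption that 0.375 is a standardised difference in an unadjusted two-group comparison. With 74 recruits, power is about 62% to 66% instead of 80%, and the effect detectable at 80% power is about 0.46 to 0.44 instead of 0.375. Even 89 v 89 gives only about 70%. Any loss among the 74 would lower these figures further.

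The 89 and 74 need reconciling, but that discrepancy does not cause the shortfall: with 74 recruits, choosing one pilot size over the other moves power by about 4 percentage points (62.0% to 65.9%). The documents do not show that the control group is biased or selected, and no such conclusion is drawn here.

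**What to change.** In the Analyses section:

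1. State which pilot patients supply the FCR7 comparator, how many they are, and how 74 relates to the 89 in the Background.
2. Remove the claim that the target matches the pilot cohort if the two numbers do not match.
3. Name the metric of the 0.375. Then either restate the effect detectable at 80% power for the comparator actually used (about 0.46 against 74, about 0.44 against 89), or keep 0.375 and give the corresponding power (about 62% or 66%), or state the baseline or repeated-measures correlation that would justify 0.375 at 80%, with its source.

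The recruitment target need not change, since this is a single-centre pilot that is also assessing feasibility. The cost is a few sentences and one recalculation. The only downside is a less favourable planning figure.

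### The sample-size statement (74 patients, effect 0.375, 80% power) is not supported by its stated inputs: two cohorts of 74 give about 62% power unadjusted, and no variance reduction is stated

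*Protocol article*

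**What the plan says.** All the sample-size inputs are in the Analyses section of the protocol article. Outcomes of patients whose radiographers have had the training are to be compared with those of the pilot cohort, treated at the same institution before the training existed. On size it says that "the aim is to recruit 74 patients so that an effect of 0.375 (medium to low) can be detected at 80% power", a number chosen to match the pilot cohort. The test is two-sided at alpha 0.05, and its purpose is to judge the training's effect on FCR levels. The effect is 0.375, described as medium to low, with no unit.

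The same section plans a latent growth curve analysis of FCR trajectories and the inclusion of covariates to control for differences between the cohorts. Neither is linked to the power sentence, and no SD, correlation or method is given for it.

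Three statements elsewhere bear on the figure:
- The Abstract makes FCR7 the primary outcome.
- Phase 3—Evaluation schedules FCR7 at planning (t1), weekly during radiotherapy, at the end of treatment (t3) and six to eight weeks later (t4).
- The Background gives a different pilot count: "FORECAST analysed conversations between 89 patients and their radiographers during the weekly review appointments".

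**The concern.** The power sentence fixes the sample size, effect, power, alpha and sidedness, and the sentences before it fix the comparison. With that much stated, the figure should be reproducible, and for a plain comparison of two cohorts it is not. The gap is about 18 percentage points of power, too large for rounding or a choice of approximation.

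This is the only quantitative basis the article gives for 74 patients. If no variance reduction lies behind it, a true effect of 0.375 would be missed about 38% of the time, not the 20% implied. The study is meant to prepare for a multi-centre randomised trial, so whoever plans that trial needs to know what this comparison could detect, and under which analysis.

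**Working it through.** **Inputs.** From Analyses: 74 in the new cohort; 74 in the pilot cohort (read from "Matching the sample size of the pilot study cohort"); effect 0.375; power 80%; two-sided alpha 0.05. Assumption: 0.375 is a standardised mean difference (SD = 1), the natural reading of the label medium to low for a continuous score.

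**1. Attempt to reproduce the stated figure, 74 v 74, normal approximation.**
- Standard error = √(2/74) = 0.1644.
- Power at 0.375 = Φ(0.375/0.1644 − 1.960) = Φ(0.321) = 62.6%.
- Detectable effect at 80% power = (1.960 + 0.842) × 0.1644 = 0.461.
- Number per cohort for 0.375 = 2 × (2.802/0.375)² = 111.6, so 112.

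The noncentral t gives 62.0%, 0.464 and 112.6, so 113 per cohort. The pilot is already complete. With its size held at 74, the new cohort would need 1/[(0.375/2.802)² − 1/74] = 227.1, so about 228.

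**2. Other readings that need no variance assumption.**

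| Reading | Power at 0.375 | Needed for 80% power, or detectable effect |
|---|---|---|
| 74 v 89 (all pilot patients in the Background) | 66% | detectable 0.443 |
| 89 v 89 | 70% | detectable 0.422 |
| One-sided 0.05, 74 v 74 (against the text) | 73% | detectable 0.411 |
| 74 in total, 37 v 37 | 36% | detectable 0.660 |
| One-sample or paired, n = 74 | 89% | needs 58; detectable 0.330 |
| 0.375 as a correlation | – | needs about 54 in total |
| 0.375 as Cohen's f (d = 0.75) | – | needs about 29 per cohort |

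None yields 74, 0.375 and 80% together.

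**3. Variance reduction that would reach it (74 v 74).** The residual variance, as a fraction of the raw variance, must be at most (0.375/0.4636)² = 0.654.
- *One post-baseline FCR7 adjusted for t1:* the factor is 1 − r², so r ≥ √(1 − 0.654) = 0.59 (0.58 by the normal approximation). By the normal approximation, power is 67% at r = 0.3, 75% at 0.5, 81% at 0.6 and 89% at 0.7.
- *Mean of m scores, no baseline:* the factor is [1 + (m − 1)ρ]/m. The correlation must be at most 0.48 for m = 3, 0.57 for m = 5 and 0.59 for m = 6.
- *Mean of m post-baseline scores adjusted for t1, equal correlation ρ throughout:* the factor is [1 + (m − 1)ρ]/m − ρ². For m = 2 it is largest at ρ = 0.25: 0.625 − 0.0625 = 0.5625. The worst-case detectable effect is then 0.4636 × √0.5625 = 0.348. For m = 3 the worst case is 0.309, and for m = 5 it is 0.278.

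So whether 0.375 is reachable depends on a model and on correlations that the power statement does not give.

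**4. Recruited or analysed.** The 74 is a recruitment target, and retention is something the study will measure ("participant recruitment and retention rates will be calculated"). The article gives no loss figure. If 10% to 25% of the new cohort were lost (assumed range), unadjusted power at 0.375 against 74 pilot patients would be 60% to 55%.

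**The case against.** The strongest reply is that an unadjusted t-test on one score is not the planned analysis. Analyses plans a growth curve and covariate inclusion, and FCR7 is measured repeatedly from t1 to t4. Step 3 shows how much this can matter: under equal correlation and a constant effect, two post-baseline scores adjusted for t1 detect 0.348 or less at 80% power whatever the correlation. Even with an assumed 15% loss (63 v 74) the worst case is 0.363, still below 0.375.

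That stands, and it rules out two stronger readings. A reader might infer that the study is simply underpowered for 0.375; the documents do not show this, because the planned analysis could supply the missing precision. A reader might also infer that a baseline correlation of 0.59 is the only way to 80%; that threshold applies only to a single post-baseline score.

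The reply does not rescue the sentence as written. Covariates are introduced to control cohort differences and the growth curve to describe trajectories; neither is offered as a basis for power. T1 FCR7 is not named as a covariate, and the article does not say that the pilot holds comparable repeated FCR7 scores. In non-randomised cohorts that differ on a covariate, adjusting for it also costs some precision, so the full gain cannot be presumed.

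A second reply is that a condensed article may leave correlations and attrition allowances to the full protocol. As a complaint about omission that would succeed. Here, though, the article makes a definite numerical claim that its own inputs do not yield.

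**Conclusion.** The power statement is wrong as written, in the sense that its stated inputs do not support it. For two independent cohorts of 74, two-sided 0.05, power at 0.375 is about 62% and the effect detectable at 80% power is about 0.46 SD; 0.375 needs 113 per cohort, and using 89 pilot patients gives only 66%. This rests on reading 0.375 as a standardised mean difference and on all 74 being analysed. The figure becomes attainable only with variance reduction from baseline adjustment, repeated FCR7 measures or both, which is unstated.

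This should be fixed, but it does not undermine the study. Phase 3 is a single-centre pilot concerned largely with acceptability and feasibility, and no decision rule in the article hangs on the FCR7 test. A reader might infer that a null result would be taken to exclude an effect of 0.375; nothing in the article says so.

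**What to change.** Keep 74 patients and change the sample-size sentence in one of two ways.

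1. Restate the figure, for example: *74 versus 74 patients analysed gives 80% power for a standardised difference of 0.46 in an unadjusted comparison (62% power for 0.375).*
2. Keep 0.375 and state what it rests on: the FCR7 time points used, t1 FCR7 as a covariate, the assumed correlations, and 74 as the number analysed, not recruited. A single post-baseline score adjusted for t1 needs a correlation of about 0.59. Several post-baseline scores adjusted for t1 need less, provided the pilot holds the same measurements.

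Either version should say that 0.375 or 0.46 is in SD units and confirm whether the comparison uses 74 or 89 pilot patients.

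The cost is one or two sentences and no extra patients. Under the first option the stated detectable effect looks less favourable.
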